Aggressive FRT with the aim of increasing stroke volume, with the assumption that this will improve end-organ perfusion and cellular oxygen use, may be physiologically flawed [21]. FRT into high-capacitance veins may in fact increase cardiac filling pressures faster than venous pressure due to limited diastolic compliance of the heart, thus reducing the pressure gradient driving venous return [22–24]. Increased venous pressure following FRT may reduce the gradient driving vital organ perfusion (MAP-CVP) [25]. Microcirculatory dysfunction through damage to the endothelial glycocalyx may be mediated partly by natriuretic peptides released as cardiac filling pressures increase following FRT [26–30]. The net effect of FRT in sepsis may be that it contributes significantly to end-organ oedema and dysfunction, and the progression from SIRS to multi-organ dysfunction and death [9, 10, 12, 13, 31, 32].

Limited published literature on the effect of FRT on cardiac output (CO) suggests that any effect is modest and transient. In a study of 20 adults with circulatory shock, the mean increase in CO immediately following FRT was 16 %, which decreased to 6 % above baseline after sixty minutes [33]. In a separate study, 32 adults with septic shock were found to have a mean increase in CO of 15 % immediately after FRT, which returned to 3 % above baseline 40 min after FRT (*p* < 0.001) [34]. There is no published literature on the effect of FRT on cardiac index (CI = CO/body surface area (BSA)) in children. The ability to predict the response to FRT allows the clinician to restrict this therapy only to those that are fluid responsive. Fluid responsiveness is considered an increase in cardiac output of 10-15 % in response to a fluid challenge (250–500 ml in adults) [35]. In the undifferentiated adult ICU population, as few as 50 % of patients may be fluid responsive [35]. The remainder receive all of the potential harms from FRT with none of the potential benefits. IVC ultrasound is a dynamic method for assessing fluid responsiveness using cardiopulmonary interactions [36]. In spontaneously ventilating adults, IVC collapsibility of >40 % has been shown to be predictive of fluid responsiveness, while IVC collapsibility of <15 % is predictive of being fluid unresponsive [37]. No study has validated IVC collapsibility as a predictor of fluid responsiveness in children.

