### Inclusion and exclusion criteria

Inclusion and exclusion are listed in Table 1. Inclusion criteria are based on international consensus definitions for the diagnosis of sepsis in children [38].

**Table 1 Tab1:** Inclusion and exclusion criteria

Inclusion criteria- all of: Suspected infection Temperature >38 °C or <36 °C Systemic Inflammatory Response Syndrome Tachycardia (temperature corrected heart rate >2 SD above normal for age^a^) *or* Tachypnoea (respiratory rate >2 SD above normal for age) Plan to administer a standardised fluid bolus by the treating clinician Standardised fluid bolus: 20 ml/kg of 0.9 % saline administered via manual push/pull or pressure bag (NOT by infusion pump). Exclusion criteria- any of: Underlying uncorrected structural cardiac disease Non-curative goals of therapy Non-English speaking	

^a^heart rate was corrected by 10 beats per minute for every degree celcius above 38^o^ [55]

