### Study procedure

Patients who fulfil the eligibility criteria and whose parents provide written informed consent will be entered into the study. Prior to administration of a standardised fluid bolus, transthoracic echocardiography, lung and IVC ultrasound will be performed, and vital signs recorded (Fig. 1). Five minutes and 60 min after administration of a standardised fluid bolus, the same measurements will be taken. All ultrasound measurements will be taken by the Principal Investigator (PI), who has a Post Graduate Certificate in Echocardiography through The University of Melbourne, Australia. Recorded echocardiograms will subsequently be assessed by a blinded paediatric cardiologist. Lung ultrasound and IVC ultrasound will be assessed by a blinded paediatric emergency physician with a Diploma in Diagnostic Ultrasound (Australian Society for Ultrasound in Medicine). Vital signs that will be recorded from the patients monitor (Phillips MP70, Phillips Healthcare, Andover, MA) include: heart rate (HR), respiratory rate (RR), blood pressure (BP), and peripheral oxyhaemoglobin saturation (SpO2). Additionally, patient temperature in degrees celcius will be recorded and a 10 s video recording of the patient will be taken at each time point and used to assess conscious state, capillary refill, and respiratory effort. These video recordings will be scored in terms of Glasgow Coma Scale for conscious state, time in seconds for capillary refill, and Silverman Score for respiratory effort [39] by a blinded paediatric emergency physician. Final outcomes will be obtained from the patient medical record following discharge or death.

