### Study flow chart

#### Outcome measures

*The primary outcome measure* is the percentage change in CI 5 and 60 min after standardised fluid bolus administration compared to baseline.

*Secondary outcome measures* include the change in EVLW after standardised fluid bolus administration, whether IVC collapsibility is predictive of fluid responsiveness, and whether the observed change in cardiac output following standardised fluid bolus administration is correlated with changes in vital signs and clinical observations. We also collected the following outcome data: ICU admission, requirement for inotrope/vasopressor infusion, requirement for non-invasive or invasive ventilation, requirement for renal replacement therapy, requirement for extracorporeal membrane oxygenation (ECMO), final microbiological diagnosis, and mortality.

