### Sample size, power, and statistical methods

For a precision based sample size estimation based on the continuous outcome variable of change in cardiac output following standardised fluid bolus administration, the following assumptions have been made: a mean increase in cardiac output of 20 % with a standard deviation of 10 %, a precision of the study tool (echocardiogram) of +/− 2 %. For a precision estimate of 5 %, a sample size of 50 would be required. This would also allow for regression analysis of several suspected confounding variables, including age, underlying illness aetiology (respiratory vs non-respiratory), and total volume of fluid previously administered.

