### Limitations

Ultrasound-based assessments are user-dependent. As such, they are prone to variability both within and between sonographers. Ultrasound-based assessment of EVLW and fluid responsiveness based on IVC collapsibility have been validated in adult patients but not in children. Age-based physiological differences in children may limit their utility in the study population. Some vital signs recorded (such as capillary refill, conscious state, and respiratory effort) are qualitative and prone to bias. Efforts to minimise the impact of potential bias on the study results include video recording of the patient at each time point and subsequent assessment blinded to the timing of the video recording relative to the timing of fluid bolus administration. At the time of assessment, enrolled patients are undifferentiated and are being treated empirically for sepsis. They may have an alternate final diagnosis. At the time of enrolment, patients are receiving multiple interventions, some of which are distressing and make ultrasound assessment challenging. Interventions other than fluid bolus administration (such as the use of non-invasive or invasive ventilation, or administration of inotropic or vaso-active therapies) may confound the study results. To minimise the effect of other therapies on study results, the study will focus only on the first hour of resuscitation. Any other interventions performed during the study period will be recorded. The study will only recruit patients when the PI is available in the ED. This limits the total number of patients recruited and the time of day when patients are recruited.

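### Children who have already had a bolus can be enrolled; if it was recent, the measured change in cardiac index may be biased downward, mainly at 60 min, and adjusting for previous volume alone cannot remove this

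*Protocol article*

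**What the plan says.** All places are in the protocol article.

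- **Eligibility (Inclusion and exclusion criteria, Table 1).** The only fluid criterion is "Plan to administer a standardised fluid bolus by the treating clinician". The exclusions read "Exclusion criteria- any of: Underlying uncorrected structural cardiac disease Non-curative goals of therapy Non-English speaking"; none concerns earlier fluid.
- **Baseline (Study procedure).** "Prior to administration of a standardised fluid bolus, transthoracic echocardiography, lung and IVC ultrasound will be performed". The reference point is therefore the study bolus, whether or not fluid came before it.
- **Primary outcome (Outcome measures).** "percentage change in CI 5 and 60 min after standardised fluid bolus administration compared to baseline".
- **Earlier fluid (Sample size, power, and statistical methods).** The sample of 50 is described this way: "This would also allow for regression analysis of several suspected confounding variables". One of the variables named is "total volume of fluid previously administered". Time since that fluid is not named.
- **Decay of a bolus effect (Background).** In a study of 20 adults, "the mean increase in CO immediately following FRT was 16 %, which decreased to 6 % above baseline after sixty minutes". In a second study, of 32 adults, a 15 % rise had fallen to 3 % at 40 min. The article says that nothing comparable is published for CI in children.
- **Window (Limitations).** To limit the influence of other therapies, "the study will focus only on the first hour of resuscitation". Earlier fluid is not among the limitations discussed.

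**The concern.** The authors expect some children to have had fluid before the study bolus, and expect it to matter. If that fluid was a bolus shortly before the baseline scan, the Background figures mean that the child starts the study hour with CI temporarily raised. As that rise fades, it is subtracted from the effect of the study bolus. The loss is larger at 60 min, when more of the earlier effect has gone.

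The stated provision is a regression on previous volume. Carry-over is driven by elapsed time: the same volume finished 10 min ago and finished 2 h ago leaves very different residues at baseline, and volume takes the same value in both cases.

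The bias runs toward the modest, short-lived effect that the Background anticipates. A sustained effect at 60 min could look smaller than it is, or absent, for reasons that depend on who was enrolled as well as on physiology. The Discussion expects the results to inform questions of fluid volume and the design of later trials.

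**Working it through.** The plan gives no figure for carry-over, so this is an illustration built on its own decay figures. It does not depend on how the sample size of 50 was reached.

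**Inputs from the Background.** Study A (20 adults): +16 % falling to +6 % at 60 min. Study B (32 adults): +15 % falling to +3 % at 40 min.

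**Assumptions.** Exponential decay through each pair; additive effects; one earlier bolus with the same average effect as the study bolus; study bolus given over 10 min. The plan gives neither the duration of the study bolus nor the gap from the end of the earlier bolus to the baseline scan, so the gap is varied.

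**Decay rates.**
- A: k = ln(16/6)/60 = 0.0163 per min, half-life 42 min.
- B: k = ln(15/3)/40 = 0.0402 per min, half-life 17 min.

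**Formula.** Let e(t) = e0 × exp(-k × t), in percent of untreated CI. At m min after the study bolus:
- true effect, compared with no study bolus: e(m)
- observed change: [100 + e(m) + e(gap + 10 + m)] / [100 + e(gap)] - 1
- bias: observed change minus true effect

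**Worked case, 10-min gap, 60-min scan.**
- A: e(10) = 13.59, e(60) = 6.00, e(80) = 4.33. Observed = 110.33/113.59 - 1 = -2.9 %, against a true +6.0 %. Bias -8.9 points.
- B: e(10) = 10.03, e(60) = 1.34, e(80) = 0.60. Observed = 101.94/110.03 - 1 = -7.4 %, against a true +1.3 %. Bias -8.7 points.

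**Bias per pre-bolused child, in percentage points.**

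| Gap to baseline scan | 60 min, A | 60 min, B | 5 min, A | 5 min, B |
|---|---|---|---|---|
| 10 min | -8.9 | -8.7 | -4.4 | -5.2 |
| 30 min | -6.6 | -4.1 | -3.3 | -2.5 |
| 60 min | -4.2 | -1.3 | -2.1 | -0.8 |
| 120 min | -1.6 | -0.1 | -0.8 | -0.1 |

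Taking 15 min for the study bolus changes the 60-min values little (for example -6.8 and -4.1 at a 30-min gap).

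**Pooled mean at 60 min.** The shift is the share pre-bolused times the bias per child. The share is not given; 20 % to 50 % is an assumption.
- 10-min gap: 0.20 × -8.69 = -1.7 to 0.50 × -8.87 = -4.4 points.
- 30-min gap: 0.20 × -4.09 = -0.8 to 0.50 × -6.62 = -3.3 points.

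For scale, with the plan's SD of 10 % and n = 50, the 95 % half-width is 1.96 × 10/√50 = 2.8 points. The pooled shift may fall on either side of that.

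**The case against.** A reader might infer that the 60-minute result is biased downward as a matter of fact. The documents do not support that. They give neither the share of children with earlier fluid nor the gap before the baseline scan, and earlier fluid need not have been a bolus. The decay curves rest on two group means each, in adults. Children judged to need another bolus may also be those in whom the previous one did little; the Background says that as few as half of adult ICU patients may be fluid responsive. Any of these could make the bias small. All of this stands: it limits the size that can be claimed, though not the direction if a recent effective bolus was given.

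It is also fair that the plan already treats earlier fluid as a confounder, and that the coding of a covariate is commonly left to a fuller document. The article does not say whether volume would be expressed per kg, nor whether the primary estimate is adjusted, so neither can be called an error. But the covariate that is named is a volume, and no scaling of volume carries the time information.

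The first-hour statement in Limitations might be read as ruling out an earlier bolus, or as plainly wrong. Neither reading is secure. Taken literally, a bolus plus 60 min of follow-up fills that hour and leaves little room for earlier boluses, yet Table 1 does not enforce this and the covariate list expects earlier fluid. The wording is unclear and needs reconciling.

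Finally, change from the pre-bolus scan is a legitimate outcome, close to how fluid responsiveness is judged. Moving the main estimate to a subset of unknown size would be a trade-off and does not follow from this point.

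**Conclusion.** The point holds as a conditional one. The eligibility rule, the baseline scan and the definition of the primary outcome together allow carry-over from a recent earlier bolus, and the named covariate cannot remove it. Under the adult decay figures, the 60-min bias per pre-bolused child runs from about -9 points at a 10-min gap to between 0 and -1.6 at 2 h. The 5-min bias has the same sign and is smaller. At short gaps the bias can exceed the 60-min effect itself (+6.0 % or +1.3 % in the two curves).

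This rests on adult decay, additivity, an average response to the earlier bolus and an assumed bolus duration. The effect on the overall mean cannot be stated without the share pre-bolused and the gaps. It is a cheap improvement to the plan and does not invalidate the design.

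**What to change.** Keep enrolment and the primary outcome as they are.

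1. Record the end time of the last bolus given before the baseline scan.
2. Replace the previous-volume covariate by two: prior bolus fluid in ml/kg, and minutes from the end of the last bolus to the baseline scan, with an indicator for no prior bolus.
3. Report the 5- and 60-min change separately for children with no prior bolus and with a prior bolus, alongside the overall result. Do not split at a 60-min washout: at a gap of exactly 60 min the illustration still leaves -1.3 to -4.2 points at the 60-min scan.
4. Reconcile the first-hour statement in Limitations with Table 1 and the covariate list, so that it is clear whether the window starts at the study bolus or at the start of resuscitation.

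**Cost.** One extra time field and some analysis wording. Intervals are wider in the no-prior-bolus group: at SD 10 %, the 95 % half-width goes from 2.8 points with 50 children to 1.96 × 10/√40 = 3.1 if 20 % are pre-bolused, or 1.96 × 10/√25 = 3.9 if half are.

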### Limitations

Ultrasound-based assessments are user-dependent. As such, they are prone to variability both within and between sonographers. Ultrasound-based assessment of EVLW and fluid responsiveness based on IVC collapsibility have been validated in adult patients but not in children. Age-based physiological differences in children may limit their utility in the study population. Some vital signs recorded (such as capillary refill, conscious state, and respiratory effort) are qualitative and prone to bias. Efforts to minimise the impact of potential bias on the study results include video recording of the patient at each time point and subsequent assessment blinded to the timing of the video recording relative to the timing of fluid bolus administration. At the time of assessment, enrolled patients are undifferentiated and are being treated empirically for sepsis. They may have an alternate final diagnosis. At the time of enrolment, patients are receiving multiple interventions, some of which are distressing and make ultrasound assessment challenging. Interventions other than fluid bolus administration (such as the use of non-invasive or invasive ventilation, or administration of inotropic or vaso-active therapies) may confound the study results. To minimise the effect of other therapies on study results, the study will focus only on the first hour of resuscitation. Any other interventions performed during the study period will be recorded. The study will only recruit patients when the PI is available in the ED. This limits the total number of patients recruited and the time of day when patients are recruited.

## Discussion

Four major questions remain unanswered regarding fluid resuscitation for paediatric sepsis: what is the ideal fluid content, what is the ideal fluid volume, over what time period it should be administered, and what therapeutic targets should be used to titrate therapy. This study will help answer the questions of fluid volume and therapeutic targets. Current paediatric fluid resuscitation guidelines and planned trials are based on the concept of empiric fluid loading using vital signs as a marker of response to treatment. This is despite evidence that the host response to sepsis in children is highly variable and dynamic during the disease course [45–47], and that vital signs are a poor predictor of disease severity or response to treatment [48–51]. As such, using a “one size fits all” approach to fluid resuscitation seems counter-intuitive. Alternatives include fluid responsiveness-based FRT. Data from randomised pilot studies in adults have shown fluid-responsiveness based resuscitation for sepsis allows more targeted fluid resuscitation (more aggressive in fluid responders, less aggressive in fluid non-responders), with an overall reduction in total fluid volume administered compared to standard treatment [52]. Additionally, the results of this study may suggest that routine assessment of EVLW allows for both the benefits and risks of fluid resuscitation to be included in the therapeutic equation for the individual patient. This approach has been described but not evaluated in randomised trials in adults [53].

This study may inform the design of future interventional studies in paediatric sepsis. The use of fluid-responsiveness based resuscitation limited by EVLW observed on lung ultrasound may allow targeted and individualised treatment [54]. This may help avoid the harms from overzealous fluid resuscitation in some children. Such a strategy would need to have a significant impact on patient-centred outcomes for widespread use, due to its implications for resources, training, and infrastructure required in ED’s caring for children.

## Abbreviations

BP, blood pressure; CI, cardiac index; CO, cardiac output; CVP, central venous pressure; ECMO, extracorporeal membrane oxygenation; ED, emergency department; EGDT, early goal-directed therapy; EVLW, extra-vascular lung water; FEAST, fluid expansion as supportive therapy; FRT, fluid resuscitation therapy; GCS, Glasgow Coma Scale; HR, heart rate; IVC, inferior vena cava; PI, principal investigator; RCH, The Royal Children’s Hospital; RR, respiratory rate; ScvO2, central venous oxygen saturation; SIRS, systemic inflammatory response syndrome; SMD, septic myocardial dysfunction; SV, stroke volume
